### Study Design

#### Cluster Randomized Trial Design

Forty rural health facilities and their catchment areas (*clusters*), 20 per region, will be randomized to an (A) early or (B) delayed onset study arm (Figure 2). From each cluster, 3 cohorts of 10 mother-child dyads (1 retrospective cohort and 2 prospective cohorts) will be enrolled into the study. For the retrospective cohort, 400 mothers of children aged 12 to 23 months (10/cluster) will be enrolled as a cross-sectional sample for retrospective assessments of children’s vaccination records during the first year of life. These cohorts, denoted by A1 and B1, will be part of the care-as-usual control group. For the longitudinal prospective cohort, 800 pregnant women in their last trimester of pregnancy will be enrolled during 2 rounds of enrollment (10 women/enrollment round/cluster) for prospective assessments of their children’s vaccination records during the first year of life. These cohorts are denoted by A2, A3, B2, and B3. In the first round of enrollment, 200 (50%) of the 400 prospective participants (those enrolled from early onset clusters; A2) will receive the intervention, and the other 200 (50%) participants (B2) will be part of the care-as-usual control group. In the second round of enrollment, all 400 participants (A3 and B3) will receive the intervention. In total, vaccination uptake and timeliness will be observed for 1200 children (n=600, 50% intervention group children and n=600, 50% nonintervention group children) during their first year of life. The nonintervention group children represent the *care-as-usual* control group in the trial.

The trial design, which analytically resembles a difference-in-difference design, allows for an analysis of the effectiveness of the intervention even in the context of contemporaneous changes in the rate and timeliness of vaccinations at the national level (eg, through national vaccination campaigns or changes in the vaccination schedule).

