### Statistical Power

The aim 1 cluster randomized trial will include 1200 women, enrolled from 40 different clusters, across 3 distinct enrollment phases, with 10 women enrolled from each cluster in each phase. This equates to k=120 statistical clusters with n=10 women per cluster. Half of these clusters (k=60/120, 50%; n=600/1200, 50%) will be allocated to the intervention arm and half to the control arm. Assuming that the primary outcome—the timeliness of the Penta3 vaccine—has an SD of 28 days, the power of the trial to detect an intervention-related difference of 7 days is 0.95 with an intracluster correlation coefficient of 0.05; the power is 0.88 with an intracluster correlation coefficient of 0.10.

The aim 2 qualitative formative work will yield data from IDIs with key informants (n=12), facility-based health workers (up to n=40), CHWs (up to n=80), and mothers (up to n=60). Prior research suggests that thematic saturation can be achieved with 12 interviews, with metathemes presenting as early as 6 interviews [23-25]. Thus, these proposed sample sizes should be sufficient to achieve thematic saturation of implementation barriers and residual barriers to timely and equitable vaccinations, as well as to identify any regional variation in reasons for delayed vaccinations.

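### The stated power of 0.95 and 0.88 holds only for a pooled comparison with no secular trend; once phase effects are allowed for, power for 7 days is 0.44 to 0.63

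*Protocol article*

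**What the plan says.** The Statistical Power section treats every facility-by-phase cell as a cluster: "This equates to k=120 statistical clusters with n=10 women per cluster". It continues: "Half of these clusters (k=60/120, 50%; n=600/1200, 50%) will be allocated to the intervention arm and half to the control arm". The primary outcome, days of Penta3 delay, is assumed to be one that "has an SD of 28 days". The section then states that "the power of the trial to detect an intervention-related difference of 7 days is 0.95 with an intracluster correlation coefficient of 0.05" and that "the power is 0.88 with an intracluster correlation coefficient of 0.10". It gives no alpha and no correlation between phases within a facility.

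The Cluster Randomized Trial Design section describes the allocation. "Forty rural health facilities and their catchment areas", 20 per region, "will be randomized to an (A) early or (B) delayed onset study arm". Of the retrospective cohorts it says: "These cohorts, denoted by A1 and B1, will be part of the care-as-usual control group". In the first prospective round A2 receives the intervention and B2 does not. In the second round A3 and B3 both receive it. The same section likens the design to difference-in-difference and says that it supports an effectiveness analysis even if vaccination changes nationally during the study.

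The section on quantitative analysis of effectiveness calls a simple comparison of means between intervention and nonintervention children unbiased because of the randomization. It plans robust standard errors clustered by facility and enrollment time.

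**The concern.** The power calculation is for a parallel trial of 60 against 60 cells. In this trial, exposure in 80 of the 120 cells is fixed by the phase: all 40 phase 1 cells are control and all 40 phase 3 cells are intervention. Randomization separates the arms only in phase 2. Of the 600 control children 400 come from phase 1, and of the 600 intervention children 400 come from phase 3, so the pooled contrast is largely a comparison of earlier with later children.

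The pooled contrast therefore has the stated power but no protection against a time trend. An analysis that has the protection claimed in the design section does not have the stated power. At stake is how a null result is read. The stated chance of missing a true 7-day effect is 5% to 12%. If phase is allowed for, it is 37% to 56%.

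**Working it through.** **Inputs.** From Statistical Power: difference 7 days, SD 28 (variance 784), 10 children per cell, ICC 0.05 or 0.10. From Cluster Randomized Trial Design: 40 facilities, exposure by phase A = (0, 1, 1) and B = (0, 0, 1). There are 20 facilities per arm, because each of four districts gives 10 clusters split by odd and even rank (Cluster Randomization). Assumed: two-sided alpha 0.05, normal approximation, outcome observed for all 10 children per cell. Power = Φ(7/SE − 1.96).

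**Step 1: the stated figures.** Take a parallel comparison of 600 with 600 children and design effect 1 + 9 × ICC, which is 1.45 or 1.90. Then SE = √(2 × 784 × design effect / 600).
- ICC 0.05: SE 1.947, power 0.949.
- ICC 0.10: SE 2.228, power 0.881.

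Both match the document. One-sided testing would give 0.975 and 0.933, which do not match.

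**Step 2: a model with phase effects.** Let c be the share of the facility correlation that persists between phases (cluster autocorrelation). The document does not give it, so c runs from 0 to 1. For the three cell means of one facility, the shared variance is a = 784 × ICC × c. The cell-specific variance is b = 784 × ICC × (1 − c) + 784 × (1 − ICC)/10.

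With a free effect for each phase, only the difference between the arm means in each phase carries information on the intervention. Its expectation is (0, effect, 0). Generalized least squares gives

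SE² = b(b + 3a) / [10(b + 2a)].

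Phases 1 and 3 thus help only as facility-level covariates, through a.

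- ICC 0.05, c = 0: a = 0, b = 113.68, SE² = 11.368.
- ICC 0.05, c = 1: a = 39.2, b = 74.48, SE² = 74.48 × 192.08 / 1528.8 = 9.358.
- ICC 0.10, c = 0: a = 0, b = 148.96, SE² = 14.896.
- ICC 0.10, c = 1: a = 78.4, b = 70.56, SE² = 70.56 × 305.76 / 2273.6 = 9.489.

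| c | SE, ICC 0.05 | Power | SE, ICC 0.10 | Power |
|---|---|---|---|---|
| 0 (same as A2 versus B2 alone) | 3.372 | 0.546 | 3.860 | 0.442 |
| 0.5 | 3.285 | 0.568 | 3.642 | 0.485 |
| 0.8 | 3.164 | 0.600 | 3.344 | 0.553 |
| 1 | 3.059 | 0.629 | 3.080 | 0.623 |

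A t reference with 38 degrees of freedom lowers each power by about 0.02.

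**Step 3: detectable difference.**
- 80% power, 2.80 × SE: 8.6 days (SE 3.059) to 10.8 days (SE 3.860).
- 90% power, 3.24 × SE: 9.9 to 12.5 days.

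**Step 4: does counting 120 clusters cause the loss?** For the pooled comparison without phase effects, SE² = (a/9 + b/3)/10. Going from c = 0 to c = 1, power rises from 0.949 to 0.984 at ICC 0.05 and from 0.881 to 0.974 at ICC 0.10. Treating the cells as independent is conservative for that comparison. The whole loss arises in Step 2.

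**Step 5: what the pooled comparison absorbs.** The mean phase of intervention children is (2 + 3 + 3)/3 = 2.67. That of controls is (1 + 1 + 2)/3 = 1.33. The contrast takes up 1.33 times any linear change per phase. As an illustration only, a trend of 5 days per phase would appear as a 6.7-day effect.

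**The case against.** The strongest defense is that the power section matches the first analysis described. The pooled comparison of means, with standard errors clustered by facility and time, is the analysis for which 0.95 and 0.88 are right. No passage specifies fixed phase effects. The multivariable analysis is an accelerated failure time model that adjusts for season and other correlates, whereas the figures above are for a linear model of delay in days. The exact treatment of period may stand in an analysis plan that is not shown.

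Part of this stands. There is no arithmetic error, and the phase-adjusted model is inferred from the claim that the design withstands contemporaneous change; it is not quoted from the article. The defense does not rescue the stated figures, however. They need an assumption of no trend that the power section never states and that the design section says is unnecessary.

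A reader might also infer that power is inflated because 120 clusters were counted where 40 were randomized. Step 4 shows the opposite for the pooled comparison, so replacing 120 with 40 in the same formula would misdirect the correction. Likewise, a reader might settle on 0.55 to 0.63 as the true power. At ICC 0.10 the lower end of that range needs a cluster autocorrelation of about 0.8 or more, and nothing in the document supports a particular value.

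**Conclusion.** The concern holds as a mismatch between the power calculation and the design that the article claims. Power of 0.95 and 0.88 for 7 days is correct only for the unadjusted pooled comparison with no secular trend. With phase effects it is 0.55 to 0.63 at ICC 0.05 and 0.44 to 0.62 at ICC 0.10, below 0.65 at every between-phase correlation.

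That power is overstated for a trend-robust analysis is firm. Where it lies within 0.44 to 0.63 is not, because the between-phase correlation is unknown. The range also rests on the assumed alpha, on SD 28, and on complete outcome data for 10 children per cell. Children who never receive Penta3 or have no record would lower it further. The document does not support the stronger conclusion that the trial must enroll more participants: the defect is in what is stated about power.

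**What to change.** Recalculate power for two sequences and three phases, 20 facilities per sequence and 10 children per cell, with phase effects. State alpha and the assumed between-phase correlation, and show a range for that correlation. Then restate either the power for 7 days (0.44 to 0.63 over the full range) or the detectable difference (about 8.6 to 10.8 days at 80% power, 9.9 to 12.5 days at 90%).

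If 0.95 and 0.88 are kept, say beside them that they apply only to the unadjusted pooled comparison and only in the absence of a secular trend.

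The cost is a rewritten paragraph and a less favorable stated figure. The correction itself requires no added enrollment.

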### Data Analysis

#### Quantitative Analysis of Intervention Effectiveness

The primary outcome measure of interest will be a continuous measure of vaccination timeliness, expressed as the delay, in days, between the vaccination due date and the date on which the vaccination was received for the third dose of the pentavalent vaccine, Penta3, due at age 14 weeks (Table 1). The secondary and other outcome measures include the timeliness and coverage of all vaccine doses recommended by age 1 year. Owing to the randomization, a comparison of mean outcomes between participants in the intervention group and those in the nonintervention group yields an unbiased estimate of the effect of the intervention.

To control for variation in sociodemographic characteristics across participants, seasonal effects, and other potential correlates of vaccination timeliness, outcomes will also be analyzed in a multivariable regression framework using accelerated failure time models with the completed vaccination dose as the failure event, age in days describing time to failure, and membership in the intervention versus control groups as the primary covariate of interest.

Robust SEs will be estimated to account for the clustering of observations across mother-child dyads enrolled from the same geographic clusters at the same time.

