## Introduction

### Background

Globally, the number of children missing their first dose of the diphtheria-pertussis-tetanus (DPT) vaccine rose from 19 million in 2019 to 25 million in 2021 [1,2]. The vast majority (14.2 million, 78%) of such *zero-dose* children reside in 20 countries, including Tanzania [3]. As in other low- and middle-income countries (LMICs), substantial rural-urban disparities in routine childhood vaccination exist in Tanzania, with vaccination rates being lower in rural areas than in urban areas [4]. Using data from the 2015-2016 Tanzanian Demographic and Health Survey, we demonstrated gaps in vaccination coverage (receipt of each recommended vaccine dose by age 1 y) and timeliness (receipt of each vaccine dose within 28 d of the recommended age) for Tanzanian children [4]. The coverage of the first dose of the pentavalent vaccine (Penta1, which includes antigens of DPT, *Hemophilus influenzae*, and hepatitis B) was 79.4% nationally in this analysis, with the remaining 21% of children classified as zero dose [4]. We documented receipt of the third dose of the pentavalent vaccine (Penta3) in even fewer children (72.7%), suggesting dropouts in the multidose vaccine series. Finally, rural children had lower timeliness of vaccination (47.8% delayed for Penta3) than urban children (24.2% delayed for Penta3). New interventions are needed to reduce the number of children who are zero dose, receive delayed vaccines, or drop out and to close the rural-urban gap in vaccination [4,5]. Such interventions must consider multifaceted barriers to vaccination and variations in the availability of human resources and infrastructure in rural areas.

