In prior research in southern Tanzania, we identified challenges with the availability of, and access to, vaccination services, including challenges with distance and transportation to health facilities, temporary nonavailability of vaccines owing to a lack of reliable refrigeration at health facilities, and vaccine wastage policies that prevented the use of multidose vials when clinics had low volumes of children to be vaccinated [6]. Service unreliability and lack of communication about service interruptions were noted as causes of frustration among mothers of vaccine-eligible children [6]. Our research also identified vaccine hesitancy owing to vaccine-related knowledge gaps and concerns. In general, rural mothers reported more vaccine-related knowledge gaps and concerns than urban mothers [6]. Despite challenges, vaccination intention was high among mothers, and conditional incentives were identified as a potential *nudge* to increase vaccination timeliness [7,8]. In addition, a community health worker (CHW)–delivered knowledge intervention was piloted and determined to be feasible to implement in rural areas. On the basis of the findings of this formative research and other published reports [9], we designed Chanjo Kwa Wakati (*timely vaccination* in Kiswahili, the most commonly spoken language in Tanzania), a community-based digital health intervention to improve childhood vaccination coverage and timeliness. The intervention seeks to combine human resources (CHWs), low-cost digital strategies (electronic communication, digital case management, and process automation), a vaccination knowledge intervention (counseling scripts addressing specific knowledge gaps), and insights from behavioral economics (reminders and incentives) to promote timely childhood vaccination.

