### Study Setting

The study will be conducted in 4 rural districts in Mwanza and Shinyanga regions in Tanzania. Both regions have large numbers of unvaccinated or undervaccinated children. The populations of Mwanza and Shinyanga region were estimated to be 3,699,872 and 2,241,299, respectively [18]. In 2022, only 56% of children aged 12 to 23 months in Mwanza region and 32.2% of children in Shinyanga region were estimated to have received all basic vaccinations, including one dose of Bacillus Calmette-Guerin vaccine, 3 doses of polio vaccine, 3 doses of DPT-containing vaccine, and one dose of measles-containing vaccine [19]. Fewer children aged 12-23 month were considered fully vaccinated according to the national vaccination schedule shown in Table 1 (32.8% in Mwanza and 2.5% in Shinyanga) [19]. Notably, 3.3% of children aged 12-23 months in Mwanza and 14.5% in Shinyanga were reported to have received no vaccinations. [19].

**Table 1 table1:** Routine childhood immunizations recommended in Tanzania before age 1 year.

Antigen	Age at vax due date
Bacillus Calmette-Guerin (BCG) and oral polio vaccine (OPV) 0	At birth or first contact
OPV1; pentavalent vaccine comprising antigens of diphtheria, pertussis, tetanus, *Hemophilus influenza* B, and hepatitis B (Penta) 1; pneumococcal vaccine (PCV) 1; and rotavirus vaccine (Rota) 1	6 weeks
OPV2, Penta2, PCV2, and Rota2	10 weeks
OPV3, Penta3, PCV3, and injectable polio vaccine (IPV)	14 weeks
Measles and rubella 1	9 months

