### Outcomes Assessments

Vaccination outcomes are described in Table 3. Vaccination coverage and dates will be ascertained for each study child using government-issued vaccination cards, which will be photographed, scanned, or copied and entered by research staff. For the retrospective cohort, the enrollment survey will assess vaccination outcomes for the child; their participation will end after the enrollment survey. Outcome data for the prospective cohort will be collected during an endline survey 12 to 15 months after the birth of the child. All vaccination doses of all vaccination series will be tracked. For women who cannot provide vaccination cards at the time of the survey, consent will be sought to access their children’s paper-based or electronic vaccination records at their local health facility.

**Table 3 table3:** Outcome measures for the cluster randomized controlled trial.

Outcome measure	Type	Source
Timeliness of the third dose of the pentavalent vaccine, Penta3 (number of days delayed)	Primary	Vaccination cards
Timeliness of Penta3 (≤28 days delayed)	Secondary	Vaccination cards
Timeliness of all other vaccine doses recommended by age 1 y (number of days delayed)	Other	Vaccination cards
Coverage of all vaccine doses recommended by age 1 y	Other	Vaccination cards

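### The mean Penta3 delay is called unbiased by randomization, but it exists only for children who receive Penta3, which the intervention aims to change

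*Protocol article*

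**What the plan says.** In the protocol article, Quantitative Analysis of Intervention Effectiveness defines the primary outcome as Penta3 timeliness, "expressed as the delay, in days, between the vaccination due date and the date on which the vaccination was received". Table 3 under Outcomes Assessments likewise lists it as a number of days delayed, taken from vaccination cards.

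The same analysis section says that, because of randomization, "a comparison of mean outcomes between participants in the intervention group and those in the nonintervention group yields an unbiased estimate" of the intervention effect. It then adds a regression analysis, introduced to control for covariates and season, using "accelerated failure time models with the completed vaccination dose as the failure event, age in days describing time to failure".

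No section gives a delay, cap, rank or censoring age to a child known not to have received Penta3. The Missing Data subsection of the Discussion covers missing cards and missing covariates only.

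The article expects such children. Background reports Penta3 receipt of 72.7% in a 2015-2016 national survey. Study Setting reports that "3.3% of children aged 12-23 months in Mwanza and 14.5% in Shinyanga were reported to have received no vaccinations". Background also describes the intervention as "a community-based digital health intervention to improve childhood vaccination coverage and timeliness", so coverage is meant to move as well as delay.

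Statistical Power counts 1200 children, with an SD of 28 days and a 7-day difference.

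**The concern.** Randomization protects a comparison of all the children allocated. It does not protect a comparison of those who went on to have the dose when the intervention affects who they are. For children in the prospective cohorts, receipt of Penta3 comes after randomization, and raising it is one of the intervention's aims. If the intervention brings in children who would otherwise have gone without the dose, their delays enter the intervention mean and have no counterpart in the control mean.

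If these added children are vaccinated later than the rest, the mean understates the gain in children who would have been vaccinated anyway. In an extreme case it could point the wrong way. The primary result could then disagree with the coverage and 28-day outcomes, and the article does not say how such a conflict would be read. The number of children contributing to the mean would also be smaller than the power statement assumes.

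**Working it through.** The check takes the plan's comparison of 600 with 600 children as given and looks only at who has a delay value.

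**1. The stated power.** Inputs from Statistical Power: SD 28, difference 7, 60 cluster-phases of 10 children per group. Two-sided alpha 0.05 is assumed, as none is stated. SE = sqrt(2 × 28² × DE / n), with DE = 1 + (m − 1) × ICC, m children per cluster-phase and n per group.
- ICC 0.05: DE = 1.45, n = 600, power 0.949 (stated 0.95).
- ICC 0.10: DE = 1.90, n = 600, power 0.881 (stated 0.88).

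The stated figures reproduce, but only with a delay for every child.

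**2. Power if only vaccinated children contribute.** At 72.7% receipt, n = 0.727 × 600 = 436.2 per group and m = 7.27.
- ICC 0.05: DE = 1 + 6.27 × 0.05 = 1.3135, power 0.896.
- ICC 0.10: DE = 1 + 6.27 × 0.10 = 1.627, power 0.825.

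**3. What the mean among vaccinated children shows.** From the article: control coverage 0.727 and a gain of 7 days. Assumed: control mean delay 30 days, intervention coverage 10 points higher (0.827), and added children with mean delay L. The gain applies to children who would be vaccinated either way, so their mean falls to 23.

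Observed intervention mean = (0.727 × 23 + 0.10 × L) / 0.827.

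| L (days) | Intervention mean | Difference from 30 |
|---|---|---|
| 30 | 23.8 | −6.2 |
| 60 | 27.5 | −2.5 |
| 90 | 31.1 | +1.1 |
| 120 | 34.7 | +4.7 |

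The difference is zero at L = (30 × 0.827 − 0.727 × 23) / 0.10 = 80.9 days.

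**4. Dependence on the assumed coverage.** Let E be the excess delay of added children over the control mean, and c1 the intervention coverage. The excess that cancels a 7-day gain is E = 0.727 × 7 / (c1 − 0.727).
- c1 = 0.80: 69.7 days.
- c1 = 0.827: 50.9 days, which is 80.9 − 30, as in step 3.
- c1 = 0.85: 41.4 days.
- c1 = 0.90: 29.4 days.

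The more the intervention succeeds on coverage, the smaller the excess delay needed to hide its effect on delay.

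**The case against.** The article does not say that children without Penta3 will be dropped, nor that the comparison of means is the sole primary analysis. The accelerated failure time model would ordinarily keep an unvaccinated child as a censored observation, and how that is done may be left to a fuller plan. This stands: the flaw belongs to the mean comparison and not to every planned analysis. It does not rescue the statement that the mean comparison is unbiased, which the article makes outright.

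A benefit would also be visible elsewhere. Receipt within 28 days (secondary) and coverage (other) can both be defined for unvaccinated children. A simulation used exponential control delays with mean 28 days, a 7-day cut floored at zero, coverage rising from 72.7% to 85%, and added children averaging 88 days late. The mean among vaccinated children worsened from 28.0 to 31.4 days, while receipt within 28 days rose from 45.8% to 51.8%. This stands too, but those outcomes are not primary.

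A reader might infer that the trial will hide or reverse a real benefit. The documents do not support that. The control mean, the rise in coverage and the lateness of added children are all assumed. Table 2 describes reminders before each due date and a health worker contact within a week after it, so newly reached children might be vaccinated close to time. With L equal to the control mean, the observed difference is −6.2 against a true −7 days. The 72.7% is also an older national figure.

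**Conclusion.** The concern holds for the mean comparison. As defined, Penta3 delay has no value without a receipt date, and receipt is something the intervention aims to change. The claim of unbiasedness through randomization is therefore a wrong statement, not a detail left out.

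Understatement of a true gain is plausible: under the step 3 assumptions, 7 days becomes 2.5 when added children average 60 days late. Reversal is possible but conditional, needing an average above about 81 days in the same illustration. The power loss, from 0.95/0.88 to about 0.90/0.82, is modest, stays above 0.80, and depends on the national figure applying to the study districts. The power arithmetic itself is correct.

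**What to change.** - Name the planned accelerated failure time model for time to Penta3 as the primary analysis, and its time ratio as the primary effect.
- Include every child whose vaccination status is ascertained, and right-censor those without Penta3 at 365 days of age in all cohorts. A common age is needed because records are read at 12 to 23 months in the retrospective cohort and at 12 to 15 months in the prospective ones.
- Report mean delay among vaccinated children descriptively, beside coverage and receipt within 28 days.
- Remove the unbiasedness sentence, or limit it to outcomes defined for all children.
- State that the power calculation refers to a mean delay available for all 1200 children, or restate it for the new primary analysis.

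No new data are needed, but this is more than a change of wording. The effect is no longer a raw difference in days. The model treats every child as eventually vaccinated, so coverage must be shown beside it. The power basis must be restated.

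A difference in mean days restricted to age 365 would not avoid that last cost. Suppose 27.3% of children are held at 267 days (365 − 98) and the rest have mean 28 and SD 28 (assumed). The SD is then sqrt(0.727 × 28² + 0.727 × 0.273 × 239²), about 109 days and not 28. That contrast would be driven mostly by coverage and would replace the 7-day target.

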## Methods

### Study Overview and Aims

This type 1 effectiveness-implementation hybrid study [16,17] uses a cluster randomized trial to evaluate intervention effectiveness and mixed methods to describe implementation outcomes. A cluster randomized design was chosen because the delivery of the intervention is organized at the cluster level. In addition, there are ethical concerns with the randomization of intervention activities, including incentives, at the individual level in rural communities in Tanzania. The evaluation of the Chanjo Kwa Wakati intervention will be guided by the reach, effectiveness, adoption, implementation, and maintenance (RE-AIM) framework. The methods used in this study are described in accordance with the CONSORT (Consolidated Standards of Reporting Trials) checklist for cluster randomized studies (Multimedia Appendix 1). The study aims and hypotheses are described in the following subsections.

#### Aim 1

The first aim is to evaluate the effectiveness of Chanjo Kwa Wakati for increasing the timeliness of childhood vaccinations due by age 1 year compared with the standard of care. The effectiveness of Chanjo Kwa Wakati will be evaluated in a cluster randomized trial with 1200 mother-child dyads enrolled from the catchment areas of 40 rural health facilities (*clusters*) in 2 regions in Tanzania. Clusters will be randomized into an early or delayed onset study arm. The intervention will target the mother-child dyad; outcomes will be assessed at the child level. Our hypothesis is that Chanjo Kwa Wakati is effective for increasing the timeliness of childhood vaccinations due by age 1 year compared with the standard of care. The primary outcome measure used to evaluate intervention effectiveness will be a continuous measure of the timeliness of the third dose of the pentavalent vaccine (Penta3), due at age 14 weeks, and determined using the birth and vaccination dates abstracted from official vaccination cards issued for the child. A secondary outcome will be a binary measure of timeliness, defined as receipt of Penta3 within 28 days of the due date. Other outcomes measures include the timeliness and coverage of all other vaccine doses due by age 1 year.

#### Aim 2

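### The pooled intervention-versus-nonintervention mean comparison is not unbiased by randomization: exposure is tied to enrollment phase, and only 400 of 1200 children form a concurrent randomized contrast

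*Protocol article*

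**What the plan says.** Under Study Overview and Aims, the unit and object of randomization are given: "Clusters will be randomized into an early or delayed onset study arm".

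The section Cluster Randomized Trial Design fixes exposure by cohort. On the retrospective cohorts: "These cohorts, denoted by A1 and B1, will be part of the care-as-usual control group". On the first prospective round: "In the first round of enrollment, 200 (50%) of the 400 prospective participants (those enrolled from early onset clusters; A2) will receive the intervention", while "the other 200 (50%) participants (B2) will be part of the care-as-usual control group". On the second: "In the second round of enrollment, all 400 participants (A3 and B3) will receive the intervention". The same section adds these up to 600 intervention and 600 nonintervention children. It describes the design as one "which analytically resembles a difference-in-difference design", able to assess effectiveness "even in the context of contemporaneous changes in the rate and timeliness of vaccinations at the national level".

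Quantitative Analysis of Intervention Effectiveness then says: "Owing to the randomization, a comparison of mean outcomes between participants in the intervention group and those in the nonintervention group yields an unbiased estimate". An accelerated failure time model follows. Its main covariate is intervention group membership, with adjustment for sociodemographic factors, season and other unspecified correlates. Robust SEs are clustered by geographic cluster and enrollment time. Enrollment phase is not named as a covariate.

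Statistical Power treats the 40 facilities at three phases as 120 clusters of 10, split 60 versus 60. It states power for a 7-day difference (SD 28 days) of 0.95 at an intracluster correlation (ICC) of 0.05 and 0.88 at 0.10.

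**The concern.** Randomizing the time of onset makes early and delayed clusters comparable within a phase. It does not make children of one phase comparable with children of another. The pooled groups differ in phase by construction: controls come mostly from the first phase, intervention children mostly from the last. A change in timeliness over calendar time therefore enters the difference in means as if it were effect.

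The retrospective and prospective cohorts also differ in how children enter. Retrospective families must have lived in the sampling area since the birth. Prospective families need only expect to stay, and outcomes are still sought for those who relocate. Two thirds of controls, and no intervention children, come from the retrospective cohort.

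The authors themselves name campaigns and schedule changes as possible. Data collection runs from February 2024 to July 2027, and the retrospective births are earlier still. The trial could report a benefit, or miss one, for reasons unrelated to the intervention.

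**Working it through.** **1. Phase mix** (Cluster Randomized Trial Design)

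| Phase | Intervention | Control |
|---|---|---|
| 1, retrospective (A1, B1) | 0 | 400 |
| 2, first prospective round (A2 / B2) | 200 | 200 |
| 3, second prospective round (A3, B3) | 400 | 0 |

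The concurrent randomized comparison is A2 versus B2: 400 of 1200 children.

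**2. The plan's own power.** Inputs from Statistical Power: SD 28, difference 7, 600 per group, 10 per cluster-phase. Alpha is not stated; 0.05 two-sided is assumed.
- Effective n per group = 600 / [1 + 9 × ICC] = 413.8 (ICC 0.05) or 315.8 (ICC 0.10).
- SE = 28 × √(2 / effective n) = 1.95 or 2.23 days.
- Power = Φ(7/SE − 1.96) = 0.949 or 0.881.

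Both stated powers are reproduced, so the plan powers the pooled 60-versus-60 contrast.

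**3. Bias of that contrast.** Let p1, p2, p3 be the mean delays by phase with no intervention effect; p1 includes any difference due to the retrospective cohort.
- Intervention mean = (p2 + 2·p3)/3; control mean = (2·p1 + p2)/3.
- Difference = (2/3)(p3 − p1). Phase 2 drops out.
- If the trend is linear, this is 4/3 of the change per phase.

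**4. False-positive rate.** Rate = Φ(b/SE − 1.96) + Φ(−b/SE − 1.96), with b the size of the bias and the SEs of step 2. The documents give no trend, so the total changes are assumptions.

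| Assumed change, phase 1 to 3 | Bias | ICC 0.05 | ICC 0.10 |
|---|---|---|---|
| 1 day | 0.7 days | 6% | 6% |
| 3 days | 2.0 days | 18% | 15% |
| 4 days | 2.7 days | 28% | 22% |
| 5 days | 3.3 days | 40% | 32% |

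A simulation of 4,000 null trials (ICC 0.05, 5-day total change) gave a mean pooled difference of −3.33 days and 39% rejection. A2 minus B2 averaged −0.02 days.

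**5. Power once phase is in the model.** Take three phase effects, 20 early clusters exposed (0, 1, 1) and 20 delayed clusters exposed (0, 0, 1). A cluster's effects in different phases have correlation r, assumed between 0 and 1.
- Variance of a cluster-phase mean: v = 28² × [ICC + (1 − ICC)/10].
- Covariance between phases: c = 28² × ICC × r.
- Generalized least squares variance of the effect = (1/10) × [v − 2c²/(v + c)].

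ICC 0.05: v = 113.68.
- r = 0: SE = √11.368 = 3.37, power 0.55.
- r = 1: c = 39.2, SE = √[(113.68 − 20.10)/10] = 3.06, power 0.63.

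ICC 0.10: v = 148.96.
- r = 0: SE = √14.896 = 3.86, power 0.44.
- r = 1: c = 78.4, SE = √[(148.96 − 54.07)/10] = 3.08, power 0.62.

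The r = 0 rows equal A2 versus B2 alone: 200 per group, effective n 137.9 or 105.3, power 0.546 or 0.442.

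**The case against.** The best defence is that the article is condensed. It describes a difference-in-difference logic, its covariate list is open-ended, and a fuller plan may well contain phase and arm terms. That stands as far as it goes: a reader might infer that the protection against secular change is never applied, and silence in an article does not establish that. But the sentence on the mean comparison is an assertion, not an omission. A term added to another model cannot make it true, and robust SEs change precision, not bias.

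Three other strong readings are tempting and do not hold.
- A reader might infer that any secular change is counted as effect. The phase 2 mean has weight zero, so a disturbance confined to phase 2 cancels.
- A reader might infer that the controls are a survivor sample assessed in a different way. Prospective outcomes are collected 12 to 15 months after birth and dyads with a child death are withdrawn, so both cohorts condition on survival to about one year. Both use the same vaccination cards, with facility records as backup. The residence rule and the follow-up of relocators do differ, but no size is given for either.
- A reader might infer that false positives would be near certain. A bias of the full 7-day design effect needs a 10.5-day change between phases 1 and 3 (two thirds of 10.5 is 7.0). Nothing in the documents supports a shift of that size.

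**Conclusion.** The unbiasedness statement is wrong as written and conflicts with the article's own difference-in-difference rationale. Two thirds of the difference in mean delay between phase 1 and phase 3, whether from calendar time or from cohort selection, enters the pooled estimate. The algebra needs no assumption beyond the stated allocation.

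The false-positive rates are illustrative. They rest on assumed changes and on a two-sided alpha of 0.05, and they use the SE implied by the plan, which treats the 120 cluster-phases as independent. A modest 3-day change already raises the error rate to about 15-18%.

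The stated power belongs to the pooled contrast. An estimator that removes common phase differences has an SE of about 3.1-3.4 days at ICC 0.05 and 3.1-3.9 at ICC 0.10, so its power for 7 days is about 0.55-0.63 and 0.44-0.62. Those ranges depend on the assumed between-phase correlation and on an effect that is the same in A2, A3 and B3.

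**What to change.** - Withdraw the unbiasedness sentence for the pooled contrast and report that contrast as descriptive only.
- Estimate the primary effect with fixed effects for the three enrollment phases and with cluster (or arm) effects. Name the same terms in the accelerated failure time model.
- As an alternative or a sensitivity analysis, compare A2 with B2 adjusted for the A1/B1 baseline. This does not use the fully treated third phase. More than one phase-adjusted form would answer the defect; what matters is that one is fixed in advance as primary.
- Restate the power section for the estimator chosen, with its assumed between-phase correlation.

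The cost is a wider SE (about 3.1-3.9 days instead of 1.9-2.2) and a much lower stated power. No new data are needed to correct the estimator.
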